## Methods and Analysis

### Study Design

The current study is an observational cohort study executed at the BG Hospital for Occupational Disease in Bad Reichenhall, Germany and at the Chemnitz University of Technology (TU Chemnitz), Germany. After successful screening for study eligibility, participants will complete medical, diagnostic, respiratory, neurocognitive, psychological, and physical performance measurements at four different time points (T1-T4). In addition to these, measurements using an activity sensor and a standardized interview for mental disorders will be performed at three different time points (see Figure 1). Data from the participants will be recorded over 21 months at the beginning (T1) and the end (T2) of inpatient rehabilitation. The follow-up time points 6 (T3) and 12 (T4) months after the beginning of inpatient rehabilitation consist of three examination days and will also be conducted by trained project staff at the BG Hospital for Occupational Disease Bad Reichenhall and at the TU Chemnitz.

**Figure 1 F1:**
[figure not shown]
Study design.

### Post-COVID Rehabilitation Program

All subjects will participate in a comprehensive multimodal and interdisciplinary inpatient rehabilitation program at the BG Hospital for Occupational Disease Bad Reichenhall for at least 3 weeks after their acute SARS-CoV-2 infection, depending on patients‘ individual indication and severity of disease. The BG Hospital is specialized in treatment and holistic rehabilitation of occupational respiratory diseases and post-traumatic stress disorders, as well as work-related skin diseases. An interdisciplinary team of physicians, physiotherapists, sport therapists, psychologists, social professionals, nutritionists, nurses, and medical-laboratory assistants will implement the standardized rehabilitation program for patients after acute COVID-19. In addition to initial illness-specific diagnostics and continuous adaption of pharmacological treatments, the individual rehabilitation program will also include psychological therapy, sports therapy, physiotherapy, respiratory therapy, and health promotion interventions (e.g., smoke cessation, stress management, physical activity).

Psychological therapy, physiotherapy, and sports therapy are important components of the concept for post-COVID-19 rehabilitation at the BG Hospital. After initial psychological interviews with the patients at the beginning of the rehabilitation, and depending on the individual course of the disease, previous illnesses, and psychological processing strategies, the patients will participate in the following four education groups once a week, as recommended by a psychologist: “Anxiety”, “Depression”, “Sleep & Stress”, “Cognitive Training”. The cognitive training will be pre-discussed individually and will be carried out by the patients twice a week for 10–15 min using the computer-based program “Fresh Minder 2, 3, and 4” (Version 2.7.7, Version 3.5.5, Version 4.0.8, Ditzungen, Germany). “Fresh Minder 2” can help patients train their brain performance, memory functions, as well as their concentration in a playful and fun way. The “Fresh Minder 2” program offers different training modules to exercise a wide range of cognitive skills. The program covers acoustic and visual perception, working memory, sustained attention, flexibility, memory, divided attention, control of impulse, logical thinking, changing of perspective, spatial imagination, response capacity, computing, selective attention, speech comprehension, processing speed, visual spatial operations, visual scanning, visuo-constructive skills, visuo-motor skills, and word memory/word finding. Weekly group meetings for mindfulness, art therapy, and post-COVID-19 group therapy will be automatically scheduled for all patients. Furthermore, individual psychological and psychiatric sessions will be conducted if needed.

After assessing initial physical condition (cardiovascular und motor fitness), patients will receive an individual training program with sports therapy and physiotherapy. The program includes endurance training (e.g., Nordic walking, ergometer training), strength training (e.g., medical training therapy, stair climbing exercise), training of coordination, mobility and fascia training, as well as relaxation exercises (e.g., progressive muscles relaxation). Additionally, respiratory physiotherapy (e.g., mobility and respiratory techniques, inspiratory muscle training, specific manual therapy) will help to reduce breathing resistance and support patients in practicing breathing techniques, managing breathlessness, and training respiratory muscles. In general, the improvement of body awareness to recognize individual physical potential and limits of performance, as well as to improve self-management strategies is an important aim of sports therapy and physiotherapy.

### Participants

Based on the admission lists for rehabilitation after acute COVID-19 at the BG Hospital for Occupational Disease Bad Reichenhall, all patients concerned will be contacted by a trained study nurse from the clinic to inform them about the aims and the procedure of the current study in a standardized telephone interview. If patients agree to receive more information about the study, they will be sent written informed consent forms, the declaration of data protection, and the first assessments (T1) by mail.

Eligibility for study participation will be determined by the following inclusion criteria, regardless of age, gender, and migrant background: (1) COVID-19 as a recognized occupational disease or work-related accident, (2) patients in the post-acute phase of mild, moderate, severe, or critical COVID-19 as defined by the WHO, (3) no evidence of acute infectivity with SARS-CoV-2, (4) confirmation of coverage of costs for rehabilitation by the statutory accident insurers or the employers' liability insurance association responsible for the patient, and (5) voluntary participation. Participants will be excluded from the study if they were diagnosed with severe cardiovascular, respiratory, neurological, or musculoskeletal disorders, as well as mental (e.g., major depression) or neurocognitive (e.g., dementia) disorders prior to their infection with COVID-19.

### Outcome Measures

#### Disease Progression of COVID-19 and Comorbidities

A medical anamnesis by a physician will document the disease progression of COVID-19 (e.g., mild, moderate, severe, or critical course of disease), as well as 47 scientifically identified symptoms of post-COVID using a semi-standardized interview according to the current German COVID-19 and post-COVID guidelines (39, 61). Furthermore, previous diseases, individual diagnosed comorbidities, and the individual medication schedule (name, dosage, and frequency of intake for all prescribed medication) will also be recorded during medical anamnesis. Additionally, the questionnaires (see section Measurements to Assess Work Ability) require patients to state their current treatments during acute COVID-19 (e.g., hospitalization, ICU) at time point T1 and treatments for post-COVID-19 outside of inpatient rehabilitation (e.g., subsequent treatment by the general practitioner, ambulatory physiotherapy or psychotherapy) at time points T3 and T4.

#### Diagnostic Measurements

A routine laboratory blood withdrawal will be executed (7.5 ml whole blood) at all measurements. Analyzed blood parameters will include e.g., glucose, hemoglobin A1c, MBG, uric acid, GPT (ALAT), y-GT, alkaline phosphatase, creatinine (Jaffé), GFR (arithmetically following CKD-EPI), potassium (serum), NT-proNBP, calcium, cholesterol, triglyceride, TSH (basal), and leukocytes. Additionally, we will analyze TNF alpha, IL-6, IL-10, IL-17, since the inflammatory proceedings seem to have a high impact on the course of COVID-19 (62).

#### Respiratory Measurements

We will use spirometry, the most common pulmonary function test, to monitor lung health over time (63). All participants will perform body plethysmography (Masterscreen Body/diff, Vyaire medical, Höchberg, Germany) including single breath diffusion to measure several lung function parameters, e.g., forced expiratory volume in 1 s (FEV_1_), forced vital capacity (FVC), functional residual capacity (FRC), total lung capacity (TLC), and diffusion capacity of the lung for carbon monoxide (DLCO). While breathing ambient air, capillary blood gas samples (Cobas b 221, Roche Diagnostics intern., Rotkreuz, Switzerland) will be taken at rest, during the 6MWT, and spiroergometry to record partial oxygen pressure (PaO_2_) and partial carbon dioxide pressure (PaCO_2_). Additionally, we will conduct respiratory muscle testing according to Kabitz et al. (64) to quantify impaired respiratory muscle function with, e.g., maximum static pressure of inspiration (PI_max_) and respiratory capacity (P_0.1_/PI_max_) (64).

#### Neurocognitive Measurements

##### Montreal Cognitive Assessment

Cognitive performance will be assessed using the MoCA as the primary outcome in this area of the investigation. The MoCa is a short screening tool to identify cognitive impairments in patients, i.e., in memory, attention, or executive functions. Following the recommendations by Nasreddine et al. (65), participants who reach a MoCA score between 30 and 26 points will be classified as cognitively healthy, whereas individuals with a MoCA score of 25 or lower will be considered cognitively impaired (65). To avoid learning effects, different versions of the MoCA will be implemented at different measurements points: Version 1 at T1, Version 2 at T2, Version 3 at T3, and again Version 1 at T4.

##### Trail Making Test

The Trail Making Test will be conducted to assess attention deficits, executive dysfunction, and cognitive impairments. The paper-pencil neuropsychological test procedure consists of two parts. First, the participants have to connect numbers in an ascending order, then they have to connect numbers and letters in an alternating way (66). The time in seconds subjects require to complete the tasks will be used as the outcome measure. Depending on that measured time, the subject will be categorized into one of the following groups: “perfectly normal,” “normal,” “mildly impaired,” and “severely impaired” (67).

##### Digit Symbol Substitution Test

Used as part of the Wechsler Adult Intelligence Scale, the Digit Symbol Substitution Test is a neuropsychological test of sustained attention, visual spatial skills, response speed, and set shifting. In the paper-pencil task, participants have to write down the correct symbol associated with series of numbers from 1 to 9. The total of correct matches performed within 90 s is then counted. After the test, the correct number-symbol matches will be recorded and taken as memory count for the test (68).

#### Psychological Measurements

The self-administered questionnaire battery consists of validated and reliable instruments to detect psychological disorders for, e.g., somatoform disorders, depression, anxiety, post-traumatic stress disorders, as well as fatigue and coping strategies (see Table 1).

**Table 1 T1:** Outcome measurements in the self-administered questionnaire.

**Outcome measurements**	**Instrument**
Origin, family status, household, education, employment and income, smoking, and drinking habits	Questionnaires of the German Health Interview and Examination Survey for Adults (“Studie zur Gesundheit Erwachsener in Deutschland,” DEGS) (69)
Socio-economic status	MacArthur Scale (German version) (70) Questionnaire for socio-economic status (DEGS) (71)
Activities of daily living	Baecke Questionnaire of Habitual Physical Activity (72)
Psychological well-being	Short interview for mental disorders—Open Access (Mini-DIPS-OA) (73) Patients Health Questionnaire (PHQ) (74) Hospital Anxiety and Depression Scale (HADS-D German version) (75) International Trauma Questionnaire (ITQ) (76) Somatic Symptom Disorder—B Criteria Scale (SSD-12) (77)
Fatigue	Brief Fatigue Inventory (BFI) (78) Fatigue Impact Scale (FIS) (79)
Coping	Brief COPE (80)
Quality of life	Short Form 12 (SF-12 Health Survey) (81)
Sleep quality	Insomnia Severity Index (ISI, German version) (82)
Work ability, employment	Work Ability Index (WAI, including comorbidities) (83) Brief Scale for Measuring Subjective Prognosis of Gainful Employment (SPE-Scale) (84) History of work ability and employment after acute COVID-19 (in comparison to DEGS) (71)
COVID-19 consequences on functional status	Post-COVID-19 Functional Status Scale (PCFS, German version) (85)
Post-COVID symptoms	Classification of symptom frequency [following (39)]

In addition, a psychologist will conduct a standardized interview for mental disorders with each patient at the beginning of rehabilitation (T1) and at time points T3 and T4.

#### Physical Performance Measurements

##### Spiroergometry

To assess participants' endurance capacity, the parameters oxygen intake, and ventilatory threshold will be measured using spiroergometry (Vyntus CPX, Vyaire medical, Höchberg, Germany). This is a diagnostic procedure in which increased physical strain within a ramp protocol is combined with the analysis of respiratory gases (86). The peak performance criterion is met when the participant reaches 70% of their anaerobic respiratory threshold. For this study, an “Ergoline” (Bitz, Germany) ergometer and the spiroergometry software “Masterscreen CPX” (Vyaire medical, Höchberg, Germany) will be used. During spiroergometry, an exercise electrocardiogram will be performed. Before spiroergometry, a resting electrocardiogram (Schiller AT 10 plus, Schiller Ag, Baar, Switzerland) will also be recorded.

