##### 6-Minute Walk Test

The 6MWT, as the primary outcome in this area of the investigation, was chosen to assess functional exercise capacity. This test requires a walkway that is at least a 30m long. The walking course will be marked every 2 m. A cone will be placed on the ground to mark the turning points. The test coordinator will use a stopwatch to inform the participant when 6 min are over. Before starting the test, the participant has to sit on a chair close to the course for at least 10 min. The participant will be instructed to avoid talking while walking (87, 88). The outcome measure of the 6MWT is the distance in meters covered by the participant within 6 min. The 6MWT will be combined with a blood-gas analysis (Cobas b221, Roche Diagnostics intern., Rotkreuz, Switzerland) to provide information about the gas distribution of oxygen and carbon dioxide, the pH level, and the acid-base balance (89).

Finally, gait velocity of the first 10 meters of the 6MWT will be recorded to assess functional mobility, gait, and vestibular functions. The test coordinator will measure the time the participant requires to walk 10 meters, so that the velocity in seconds per meter can be calculated (90). Gait abnormalities will also be observed.

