### Sample Size Calculation

The sample size is calculated using G^*^Power 3.1.9.4 (University of Kiel) for the expected results of physical performance (6MWT) and mental well-being (depression). While 6MWT is a standardized measurement to assess physical capacity in patients with chronic disease during rehabilitation, e.g., COPD, (87–89) it was used as the primary outcome of physical performance for sample size calculation. 6MWT was also conducted in the first inpatient rehabilitation studies with patients with COVID-19 and showed good feasibility (31, 55). Multiple regression analyses assess the baseline situation of patients after acute COVID-19 with regard to physical resilience or mental health at the beginning of the inpatient rehabilitation. Due to the novelty of the disease, there are no representative comparative values for associations between COVID-19 and physical resilience and mental health. Therefore, the calculation of sample size in the cross-sectional analysis refers to the generic effect size measure *f*^2^. According to Cohen (97), a mean effect size of *f*^2^ = 0.15 will be used to calculate the sample size. Results from studies on correlations in patients with pneumological diseases (e.g., COPD) are used to justify this selected effect size in more detail. The study by Zeng et al. (98) identified age, severity of disease, and quality of life as significant predictors for physical performance measured by 6-minute-walking-distance in patients with COPD with a medium effect size of *f*^2^ = 0.21. In a regression model, von Leupoldt et al. (99) showed that depression is one out of 6 predictors (e.g., age, gender, forced expiratory volume in 1 s) for the completed 6MWT in COPD-patients in outpatient rehabilitation with a small effect size of *f*^2^ = 0.06 (71). Due to the heterogeneity of study results, a medium effect size of *f*^2^ = 0.15 can be assumed for the calculation of sample size to present associations between physical performance and mental health. With a planned power of 80% and significance level of 5%, 92 data sets are required, considering up to 5 potential predictors (e.g., pulmonary function values, blood gas values, age).

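### The spiroergometry peak performance criterion is set at 70% of the participant's own anaerobic threshold, so it cannot mark peak performance and does not secure the parameters the test is meant to deliver

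*Protocol article*

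**What the plan says.** Under Physical Performance Measurements, the Spiroergometry section gives the purpose of the test as the assessment of endurance capacity, and says that "the parameters oxygen intake, and ventilatory threshold will be measured using spiroergometry". The loading is incremental: "increased physical strain within a ramp protocol is combined with the analysis of respiratory gases". It then sets the criterion: "The peak performance criterion is met when the participant reaches 70% of their anaerobic respiratory threshold".

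Nothing else in the article explains or alters this criterion. The Respiratory Measurements section mentions spiroergometry only as an occasion for capillary blood gas sampling. The Study Design section places the physical performance measurements at all four time points, T1 to T4.

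The test's standing among the outcomes is also clear. The 6-Minute Walk Test section says "The 6MWT, as the primary outcome in this area of the investigation, was chosen to assess functional exercise capacity", and the Sample Size Calculation section works "for the expected results of physical performance (6MWT) and mental well-being (depression"). Spiroergometry enters neither.

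**The concern.** A criterion for peak performance should separate tests in which the participant came close to their limit from tests in which they did not. This one is anchored to a point below a threshold that is itself no higher than peak. It also sits in the same short section as the statement that the ventilatory threshold is to be measured. A mark that comes before the threshold cannot show that the threshold was reached.

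At stake is the interpretation of the protocol's gas-exchange measure of endurance capacity. Physical capacity is named in the first of the main research questions, and this measure is repeated over 12 months. If the rule ends tests early, the threshold is lost. If tests run on to varying points beyond the rule, oxygen intake may partly reflect where each test ended.

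**Working it through.** No power, alpha or sample size figure is involved. The check is one of ordering.

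**Inputs from the Spiroergometry section**
- Criterion: C = 0.70 × AT, where AT is the participant's own anaerobic respiratory threshold.
- Loading: a ramp, so lower intensities are passed before higher ones.
- Parameters wanted: oxygen intake and ventilatory threshold.

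**Assumptions, because the article is silent**
- C and AT are read on one scale that rises through the ramp. The article does not name the quantity.
- AT is the participant's threshold in the test being judged.
- True peak P is at least AT.

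**Step 1: criterion against threshold.** For any AT > 0, C = 0.70 × AT < AT. The gap is (AT − 0.70 × AT) / AT = 30%, the same for every participant. On a ramp, C is reached first.

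**Step 2: criterion against peak.** Since AT ≤ P, C ≤ 0.70 × P. Write AT = x × P. The documents give no value for x, so a range is shown:

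| x = AT / P (assumed) | C / P = 0.70 × x |
|---|---|
| 0.5 | 0.35 |
| 0.7 | 0.49 |
| 1.0 (upper limit) | 0.70 |

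Even at the upper limit, the point called peak is 30% short of peak.

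**Step 3: what follows under each possible role of the criterion**
- *It ends the test.* The ramp stops at C < AT. AT is not observed, and oxygen intake is taken below the threshold. If the 70% refers to oxygen uptake, the recorded value is 30% below even the threshold value.
- *It is an effort check and the ramp continues.* AT and a higher oxygen intake may both be observed. But a test that stops anywhere between C and AT still passes as peak, so passing gives no assurance that the threshold was reached.

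**Step 4: can the criterion be applied?** During the ramp, 70% of AT can be recognised only if AT is already known, and the section describes no prior determination. Applied afterwards, it can be checked only in tests where AT was found. Every such test has already gone past 0.70 × AT, so the criterion then rejects none of them.

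**Step 5: the two threshold terms.** The parameter is called the ventilatory threshold, and the criterion uses a different term. The article neither equates nor orders the two. Steps 1 and 2 do not depend on this. The statement that the *ventilatory* threshold goes unobserved under the stopping role does depend on the two being the same point.

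**The case against.** The strongest reply is that the article says only that a criterion is met, not that the test stops there. A reader might infer that neither a peak oxygen uptake nor the ventilatory threshold can be obtained, or that up to 100% of threshold values will be missing. The text does not support that. It follows only if the criterion is an end-of-test rule, and if the ramp continues both values can be observed. This part of the objection stands.

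Three further points also stand:
- Peak oxygen uptake is not a named parameter. The article says oxygen intake, and the word peak appears only in the name of the criterion.
- Nothing shows that test termination will differ between visits. A bias in change from T1 to T4 is a possibility that the rule leaves open, not a demonstrated effect.
- Circularity bites fully only if the rule is applied during the test. Gas-exchange data could be reviewed afterwards, although Step 4 shows that the criterion then excludes no test in which the threshold was found.

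It can also be said that the sentence may be a translation slip, and that a fuller testing procedure may exist. The documents cannot settle the first. The second would excuse a missing detail, but this is a specific stated rule that conflicts with the parameters stated beside it.

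**Conclusion.** The criterion is wrong as written. A point 30% below the participant's own threshold, and at no more than 70% of true peak, cannot mark peak performance whichever role it was meant to play. Depending on that role, it either ends tests before the threshold or passes sub-threshold efforts as peak. In neither case does it secure comparable values across T1 to T4.

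The ordering rests on the ramp and on peak being no lower than the threshold. The loss of the ventilatory threshold rests on two further assumptions: that the criterion ends the test, and that the two threshold terms denote one point.

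The reach is limited. The 6MWT is the primary outcome for physical performance, and neither it nor the sample size depends on this sentence. The affected results are the spiroergometry outcomes. The point should be corrected, but it does not threaten the study's main analysis.

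**What to change.** Reconcile the criterion with the stated parameters:
- State the quantity that the 70% refers to, and whether the criterion is an effort check or an end-of-test rule.
- Use one threshold term throughout, or define both and give their order.
- Apply the same criterion at T1, T2, T3 and T4.
- Record for each test whether the ventilatory threshold was identified, and analyse that parameter only in tests where it was.
- If the test is meant to be submaximal, do not describe the oxygen intake as peak.

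The exercise limit itself is a matter for the clinical team, and none is proposed here. The cost is one corrected sentence and, if it is not already captured, one field on the test record.
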